### Hypotheses

This study has been designed to investigate four specific hypotheses relating to the effect of maternal and infant infections with geohelminths on host immune responses and development of allergic inflammatory diseases: 1) chronic exposures to geohelminth infections (i.e. maternal geohelminth infections and infant geohelminth infections within the first 2 years of life) suppress immune responses to childhood vaccines; 2) chronic exposures to geohelminth infections suppress aeroallergen skin test reactivity; 3) chronic exposures to geohelminth infections protects against the development of eczema; and 4) chronic exposures to geohelminth infections protect against the development of asthma but non-chronic exposures (i.e. later childhood exposures occurring after 2 years in the absence of maternal geohelminth infections) increase the risk of asthma.

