### Measurement and definition of geohelminth exposures

Stool samples to measure geohelminth infections have been collected from mothers in the third trimester of pregnancy (stool samples collected after birth and before the child is 14 days old are considered to represent a third trimester stool sample where the mother has not received anthelmintic treatment) and from infants at 3, 7, 13, 18, 24, and 30 months, and at 3, 5, and 8 years. Stool samples are analysed using a combination of standard methods including direct saline mounts, the modified Kato-Katz method, formol-ether concentration, and carbon-coproculture methods [45]. Geohelminth infectious exposures will be defined as follows: 1) maternal geohelminth infections-presence of any geohelminth infection detected during the 3^rd ^trimester of pregnancy; and 2) infant geohelminth infections-presence of any geohelminth infections detected during the first 2 years of life.

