### Measurement and definitions of study outcomes

#### Primary study outcomes

1. *Vaccine immune responses: *vaccine immunity will be measured by the presence of protective antibody levels measured as follows-1) IgG to tetanus toxoid as described previously [46]. Immune protection will be defined > 0.15 IU/ml; 2) titer of neutralizing antibodies to OPV type 3 using the microneutralization assay at the Health Protection Agency (HPA), London, UK. Protection will be defined as OPV type 3 virus neutralization at 100TCID50 at serum dilution ≥ 1:8 dilution; 3) IgA to rotavirus (HPA); protection indicated by titers ≥ 20 U/mL; 4) IgG to polyribosylribitol phosphate of *Haemophilus influenzae *type B (Binding site, Birmingham, UK); protection > 0.15 mg/mL; 5) anti-HBS IgG antibodies (Architect, Abbott Diagnostics, Sligo, Ireland), protection > 10 IU/mL IgG. Plasma samples collected at 24 months and 5 years will be used to measure short-term (24 months) and long-term (5 years) antibody-mediated protective immunity. Vaccine responses to Hib and rotavirus will be measured only at 7 months to distinguish vaccine-mediated responses from those acquired from natural exposures to these infections.

2. *Atopy: *defined by the presence of allergen skin test reactivity at 5 years to any of the following aeroallergens: *Dermatophagoides pteronyssinus/farinae *mix, American cockroach (*Periplaneta americana*), fungi mix, dog, cat, and mixed grass pollen. A positive test is defined by the presence of a skin wheal ≥ 3 mm greater than saline control. All skin testing will be conducted by trained physicians and will be supervised by a highly experienced clinical investigator ([name]).

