### Analysis plan

Statistical analysis will be guided by the conceptual frameworks presented for each of the study outcomes (Figures 2, 3, 4 and 5). The analysis of the primary study outcomes will use multiple logistic regression to estimate the Odds Ratios for exposure-outcome associations with adjustment for appropriate confounding factors. For example, *a priori *confounders for the association between maternal geohelminth infections and eczema by 3 years of age are gender, maternal educational level, household crowding, and infant geohelminth infections. The primary analyses will evaluate the effects of maternal geohelminth infections or infant geohelminth infections on: 1) protective immunity to common childhood vaccines: 2) the presence of allergen skin test reactivity at 5 years of age; 3) the development of eczema by 3 years of age; and 4) the development of asthma at 5 and 8 years of age. Immunological variables will be defined as binary variables with a cut-off defined by the limit of detection of the assays (i.e. IL-10) or median level (i.e. IL-8) or as log_e_-transformed continuous variables. Because immunological variables are considered as intermediate in the causal pathways between exposures and outcomes, these variables will be evaluated in hierarchical analyses [60].

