**Figure 2 F2:**
[figure not shown]
**Conceptual model for effects of maternal and infant geohelminth infections on vaccine immune responses measured at 7 months, 2 years or 5 years**. Maternal infections would be expected to mediate effects on vaccine responses at 7 months and 2 years, although infant infections, generally acquired during the second year of life, may contribute to effects at 2 years. The suppressive effects of infant infections would be expected to be most important at 5 years. Potential immunological mechanisms that may mediate the suppressive effects of geohelminth exposures are shown in dashed boxes.

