*Eczema *is a chronic relapsing inflammatory skin disease that may be caused by an impaired ability to regulate inflammation induced by environmental insults in the presence of impaired skin barrier function [122]. Eczema generally develops within the first 6 months of life [123], peaks in prevalence between 2 and 3 years [124], after which the prevalence declines [125]. Little is known of the natural history of eczema in tropical environments with respect to prevalence, severity, environmental risk factors, and associations with atopy. The association between eczema and geohelminth infection is controversial [126] and studies have shown both positive [127] and negative [128-130] associations. An intervention study in Uganda provided evidence that treatment of geohelminths during pregnancy was associated with a reduced risk of eczema at 1 year [130]. Infants of infected mothers in the placebo group had a reduced prevalence of eczema compared to those of non-infected mothers [130].

The mechanisms by which geohelminth infections may reduce the risk of eczema are not known. Possible mechanisms are illustrated in Figure 5. The strongest effects are likely to be mediated by maternal infections because the disease often appears before infant geohelminth infections are acquired. The clinical presentation of eczema is a direct consequence of the damage caused by repeated scratching of the skin. Eczema, may therefore, be caused by numerous external insults that cause pruritus. A novel finding is that children born in the rural Tropics rapidly down-regulate pro-inflammatory responses to innate immune stimuli [56]. Such age-dependent responses are likely to be important adaptive mechanisms by which an early capacity to respond to innate immune stimuli that may be important in the absence of adaptive immunity but associated with an increased risk of pathologic inflammation, is rapidly down-regulated once specific adaptive immune responses have developed. We hypothesize, therefore, that the protective effects of maternal geohelminth infections are likely to be associated with markers of early immune maturation and mediated by non-specific and generalized anti-inflammatory effects (e.g. increased spontaneous IL-10) and regulation of innate (i.e. reduced IL-8 production to TLR agonists) and adaptive (i.e. elevated frequencies of induced regulatory T cells [i.e. CD4^+^IL-10^+ ^Tr1 cells]) immunity.

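### Infant infection up to 24 months is named as an exposure for eczema counted from birth, with no rule that infection must precede onset, while Table 2 and Figure 5 use maternal infection only

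*Protocol article*

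**What the plan says.** All references are to the protocol article.

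- **Exposure.** Under Measurement and definition of geohelminth exposures, the infant exposure is "infant geohelminth infections-presence of any geohelminth infections detected during the first 2 years of life". Stools within that window are scheduled at 3, 7, 13, 18 and 24 months.
- **Hypotheses.** Hypothesis 3 is that "chronic exposures to geohelminth infections protects against the development of eczema", and chronic exposure is spelled out as "maternal geohelminth infections and infant geohelminth infections within the first 2 years of life".
- **Analysis plan.** "The primary analyses will evaluate the effects of maternal geohelminth infections or infant geohelminth infections on: 1) protective immunity to common childhood vaccines". The list continues with skin test reactivity at 5 years, eczema by 3 years, and asthma at 5 and 8 years. The pairing is not restricted by outcome or by age at measurement.
- **Eczema outcome.** Under Primary study outcomes, a child is a case after one qualifying presentation at any time up to age 3. Scheduled assessments are at 7, 13, 24 and 36 months, and clinic presentations also count.
- **Timing.** The Figure 2 legend describes "infant infections, generally acquired during the second year of life". The Discussion says "Eczema generally develops within the first 6 months of life" and adds that the disease frequently shows itself before infants become infected.
- **What points to maternal infection only.** The Table 2 eczema row lists maternal exposure, and Figure 5 models maternal infection alone.

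**The concern.** An infection cannot prevent eczema that is already present. As the Hypotheses and Analysis plan are worded, a child with eczema at 7 months who is first infected at 18 months is an exposed case. That child carries no information on protection, yet counts as evidence against it.

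Two things follow for an infant-infection odds ratio. Cases that begin before infection pull it toward the null. Any association that remains may reflect household conditions linked to both infection and eczema. Either way, the result would be reported as a primary test of hypothesis 3. The document also gives two answers on whether this analysis is primary at all, so an analyst could follow either.

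**Working it through.** **1. The plan's own figure.** Table 2, eczema at 3 years: maternal exposure, N = 1,840, 50% exposed (920 per group), 25% vs 35%, α = 0.01 two-sided.

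- SE under the null = √(0.30 × 0.70 × 2/920) = 0.02137
- SE under the alternative = √((0.25 × 0.75 + 0.35 × 0.65)/920) = 0.02124
- z = (0.10 − 2.576 × 0.02137)/0.02124 = 2.12, so power = 98.3%, against 99% stated

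The row reproduces to within a point at 50% exposed, which is the maternal prevalence. Table 2 has no infant row for eczema.

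**2. The windows side by side.**

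| Outcome | Outcome window | Infant exposure window | Order |
|---|---|---|---|
| Eczema | birth to 36 months | to 24 months | mixed; onset often first |
| Hib, rotavirus | 7 months | to 24 months | infection mostly later, if paired |
| Tetanus, hepatitis B, poliovirus type 3 at 24 months | 24 months | to 24 months | window closes with the sample |
| The same three at 5 years; skin tests at 5 years; asthma at 5 and 8 years | 5 or 8 years | to 24 months | exposure first |

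Eczema is the one outcome where the Hypotheses and Analysis plan name the infant exposure, the order is often reversed, and nothing in the text cuts the exposure at onset.

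**3. How many children are involved.** The notes to Table 2 give about 30% of children infected by 24 months (the table rows use 35%) and 30% with eczema by 3 years. If the two were independent (an assumption), the number with both, among 1,840, would be:

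- 0.30 × 0.30 × 1,840 = 166
- 0.35 × 0.30 × 1,840 = 193

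**4. Illustration of the dilution.** Let f be the share of eczema cases that begin before infection. The documents do not give f, so 30-70% is assumed. The true risk ratio for eczema beginning after infection is set at 0.70, also an assumption. With no confounding, the apparent ratio is f × 1 + (1 − f) × 0.70:

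- f = 0.3: 0.30 + 0.70 × 0.70 = 0.79
- f = 0.7: 0.70 + 0.30 × 0.70 = 0.91

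**5. What is left if exposure counts only before onset.** Informative exposed cases are (1 − f) times the numbers in step 3:

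- from 166: 116 (f = 0.3) down to 50 (f = 0.7)
- from 193: 135 down to 58

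**The case against.** The strongest reply is that the analysis is not really planned. The Analysis plan opens by tying the work to the conceptual frameworks, and the eczema framework, Figure 5, is maternal only, as is Table 2. The one worked eczema example in the Analysis plan takes maternal infection as the exposure and infant infection as a covariate. This carries weight, and it is why the point is partly one of reconciliation. It does not settle the matter. Hypothesis 3 and the list of primary analyses name infant infection outright. Table 2 is also not a complete list of primary analyses: it has no row for asthma at 8 years, and it powers skin tests at 3 years although the primary is at 5.

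It is also fair to say that some eczema does follow infection. Cases count to 36 months, the Discussion puts peak prevalence between ages 2 and 3, and it says little is known of the natural history in the tropics.

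Three stronger readings are tempting, and the documents do not support them.

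- **That infant infection will be tested against the 7-month vaccine results.** The protocol says "Vaccine responses to Hib and rotavirus will be measured only at 7 months", and the unrestricted sentence in the Analysis plan could be read as pairing these with infant infection. But the Figure 2 legend and Table 2 assign 7-month responses to maternal infection, and Table 2 sets infant infection against vaccines only at 5 years. What remains is loose wording.
- **That exposure follows outcome for most children.** Only 30-35% are ever infected by 24 months, so at most about a third could be in that position.
- **That the size of the bias is known.** It is not. Table 2 gives only maternal contrasts for these outcomes, and reusing them as infant effects would have no basis in the text.

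**Conclusion.** The concern holds for eczema. As worded, hypothesis 3 and the Analysis plan make infection at any time to 24 months a primary exposure for eczema counted from birth, and nothing restricts it to infection before onset. By the document's own account the order is often reversed, so the ever/never odds ratio cannot be read as protection, and a null result would say little about hypothesis 3. Table 2 and Figure 5 point to a different, maternal-only analysis.

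The size cannot be fixed from the documents. The range of 0.79-0.91 for a true 0.70 rests on an assumed 30-70% of cases preceding infection and on no confounding. It shows that dilution could matter, not how large it is.

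For Hib and rotavirus, only the wording needs aligning. For tetanus, hepatitis B and poliovirus type 3 at 5 years, skin tests at 5 years, and asthma at 5 and 8 years, the exposure window closes before the outcome and the point does not apply.

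**What to change.** Choose one of two for eczema, and make the Hypotheses and the Analysis plan say so.

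1. **Maternal infection only**, as Table 2 and Figure 5 already have it. Remove infant infection from hypothesis 3 and from the eczema item of the primary analyses.
2. **Keep infant infection, counted only before first eczema.** Treat it as time-updated, using the stool date against the date of first eczema. A logistic model by visit interval would still give an odds ratio. State in advance how an infection found at the same visit as first eczema is classified.

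Either way, add to the Analysis plan that 7-month Hib and rotavirus responses are analysed for maternal infection only, in line with Table 2 and Figure 2.

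The cost is wording and, for option 2, a different model. Stools and eczema assessments are already scheduled by visit, so no new data are needed. Option 2 leaves fewer informative exposed cases: about 50-135 under the assumptions above. A fixed landmark, such as infection by 13 months, would be simpler, but it would discard most infant infections, since the Figure 2 legend places them in the second year.

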**Figure 2 F2:**
[figure not shown]
**Conceptual model for effects of maternal and infant geohelminth infections on vaccine immune responses measured at 7 months, 2 years or 5 years**. Maternal infections would be expected to mediate effects on vaccine responses at 7 months and 2 years, although infant infections, generally acquired during the second year of life, may contribute to effects at 2 years. The suppressive effects of infant infections would be expected to be most important at 5 years. Potential immunological mechanisms that may mediate the suppressive effects of geohelminth exposures are shown in dashed boxes.

**Figure 3 F3:**
[figure not shown]
**Conceptual model of effects of maternal and infant geohelminth infections on allergen skin test reactivity**. The effects of both exposures are presumed to occur via the development of a modified Th2 (mTh2) response during chronic geohelminth infection. A modified Th2 response may affect allergen skin test reactivity through 2 distinct mechanisms: 1) a direct effect on mast cell function independent of aeroallergen-specific IgE resulting in an increased threshold for activation through enhanced production of spontaneous or geohelminth-induced IL-10. Such effects would be predicted to effect wheal sizes non-specifically including the histamine positive control. 2) An indirect effect on mast cell function by attenuation of the association between specific IgE and skin test reactivity. This effect would be predicted to be aeroallergen-specific, affect only those wheals for which an individual has significant levels of specific IgE (at > 0.35 kU/L) but not the positive control, and be mediated by aeroallergen-induced IL-10. The effect could also be mediated by geohelminth-induced IL-10 for aeroallergens where the IL-10-stimulating allergens share significant immunological cross-reactivity with helminth allergens.

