The immunological mechanisms by which chronic geohelminth infections may suppress IgE-mediated hypersensitivity measured by allergen skin test reactivity are illustrated in Figure 3. Maternal geohelminth infections, augmented by infections in infancy, may have indirect suppressive effects on immediate hypersensitivity responses in the skin through effects on immune homeostasis. Chronic geohelminth infections in children are associated with an increased accumulation in vitro by unstimulated PBLs of the anti-inflammatory cytokine IL-10 [50]. A previous study of children from Cameroon infected with *A. lumbricoides *and *T. trichiura *provided evidence for an inverse association between geohelminth infection intensity and immune reactivity that was associated with enhanced production *in vitro *of IL-10 and TGF- β1 by unstimulated PBLs [94]. Further, a study of children in poor neighborhoods in Salvador, Brazil has shown that the presence of detectable spontaneous IL-10 is associated with poor access to sanitation [95] and geohelminth infections in early childhood [80]. Elevated 'homeostatic' production of IL-10 by immune cells may suppress immune reactivity [5]. IL-10 has been shown previously to suppress mast cell activation [96] and be inversely associated with wheal size to allergen skin tests [97].

In populations living in environments endemic for geohelminth infections, there is a strong disassociation between the presence of allergen-specific IgE in serum and skin test reactivity to the same allergen [57,82,98,99]. Environmental exposures including geohelminth infections are likely to be major determinants of this relationship. Geohelminth infections may affect the association between allergen-specific IgE in serum and skin test reactivity through enhanced production of helminth antigen-induced [54], aeroallergen-induced [53], or spontaneous IL-10 [50]. Increased IL-10, whatever the cellular source, may suppress mast cell activation in the skin, thereby reducing the prevalence of allergen skin test reactivity. The effects of maternal geohelminth or early infant infections on levels of allergen-specific IgE are not clear. A high proportion of children living in the rural Tropics appear to have low-affinity IgE to aeroallergens (e.g. 0.35-0.7 kU/L) that can be only be partially absorbed by pre-incubation with the specific allergen [98] and may represent cross-reactive anti-helminth IgE antibodies [100,101].

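### The > 0.35 kU/L specific IgE threshold in Figure 3 admits the whole band the article says may be cross-reactive anti-helminth IgE, so the IgE-skin test association could look weaker in exposed children with no mast-cell effect

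*Protocol article*

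**What the plan says.** The Figure 3 legend sets out two routes by which chronic geohelminth infection may reduce skin test reactivity. The second is "An indirect effect on mast cell function by attenuation of the association between specific IgE and skin test reactivity". It is predicted to be specific to the aeroallergen, to "affect only those wheals for which an individual has significant levels of specific IgE (at > 0.35 kU/L", to spare the positive control, and to act through IL-10 induced by the aeroallergen.

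The Analysis plan gives the figure a working role: "Statistical analysis will be guided by the conceptual frameworks presented for each of the study outcomes".

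The Discussion, in the section on allergic sensitization, comments on IgE at this level. "A high proportion of children living in the rural Tropics appear to have low-affinity IgE to aeroallergens", described as "low-affinity IgE to aeroallergens (e.g. 0.35-0.7 kU/L) that can be only be partially absorbed by pre-incubation with the specific allergen", and the article adds that this IgE "may represent cross-reactive anti-helminth IgE antibodies". Just before that it says: "The effects of maternal geohelminth or early infant infections on levels of allergen-specific IgE are not clear".

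The primary atopy outcome (Primary study outcomes, item 2) is skin test reactivity at 5 years and does not use IgE.

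**The concern.** A threshold of > 0.35 kU/L starts where the 0.35-0.7 kU/L band starts, so essentially the whole band is classed as significant specific IgE. By the article's own account, some of that IgE may be directed at helminths. Helminth infection is also the exposure, and the Background says infection is characterized by raised IgE.

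If anti-helminth IgE lifts more exposed than unexposed children over the threshold, the exposed group gains children who are IgE-positive and skin-test-negative. The IgE-skin test association is then diluted in that group. This matches the attenuation predicted for mechanism 2, but it comes from how IgE was classified and not from any change in mast-cell function. At stake is the choice between a mast-cell explanation and an assay explanation for the same data.

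**Working it through.** The article gives no sample size, power or expected effect for the IgE-skin test association, so there is no stated figure to reproduce. The check asks how far misclassified IgE alone can move the association when mast cells behave identically in both groups.

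**Inputs from the article:** threshold > 0.35 kU/L (Figure 3 legend); possibly cross-reactive band 0.35-0.7 kU/L, given as an example (Discussion).

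**Assumed inputs, not in the article:**
- T = 0.25: share of children with true allergen-specific IgE, all above the threshold, same in both groups.
- s1 = 0.70 and s0 = 0.02: skin-test positivity with and without true specific IgE, same in both groups.
- x: share of non-sensitized children whose cross-reactive IgE exceeds 0.35 kU/L. They are skin-test positive with probability s0.

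**Formulas:**
- P(IgE+) = T + (1 - T)x
- P(SPT+ | IgE+) = [s1·T + s0·(1 - T)x] / P(IgE+)
- P(SPT+ | IgE-) = s0 in both groups. The ratio of IgE-SPT odds ratios, exposed to unexposed, is therefore the ratio of the SPT odds among IgE-positive children.

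**Main example, x = 20% exposed versus 5% unexposed:**
- Exposed: P(IgE+) = 0.25 + 0.75 × 0.20 = 0.400. P(SPT+ | IgE+) = (0.175 + 0.02 × 0.15)/0.400 = 0.178/0.400 = 44.5%. Odds = 0.178/0.222 = 0.802.
- Unexposed: P(IgE+) = 0.25 + 0.75 × 0.05 = 0.2875. P(SPT+ | IgE+) = (0.175 + 0.02 × 0.0375)/0.2875 = 0.17575/0.2875 = 61.1%. Odds = 0.17575/0.11175 = 1.573.
- Ratio of odds ratios = 0.802/1.573 = **0.51**.
- Overall skin-test prevalence = 0.25 × 0.70 + 0.75 × 0.02 = 19.0% in both groups.

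**Varying x in the exposed, with 5% in the unexposed:**

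| x, exposed | SPT+ among IgE+, T = 0.25 | Ratio, T = 0.25 | Ratio, T = 0.30 |
|---|---|---|---|
| 5% | 61.1% | 1.00 | 1.00 |
| 10% | 54.3% | 0.76 | 0.79 |
| 20% | 44.5% | 0.51 | 0.55 |
| 30% | 37.8% | 0.39 | 0.43 |

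With exposed x at or above unexposed x, the ratio runs from about 0.39 (30% versus 5%) to 1.0 (equal frequency).

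**Second set of assumptions:** T = 0.30, s1 = 0.50, s0 = 0.05, x = 40% exposed versus 10% unexposed. The odds ratio is 7.5 in exposed against 13.5 in unexposed children. SPT positivity among IgE-positive children is 28.3% against 41.5%. Overall skin-test prevalence is 0.30 × 0.50 + 0.70 × 0.05 = 18.5% in both groups.

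**Which other Figure 3 predictions could separate the explanations?** Misclassified IgE does not touch the histamine wheal, so an unchanged positive control fits both. The predicted link with aeroallergen-induced IL-10 could separate them in part. The legend's remark on cross-reactivity concerns allergens that stimulate IL-10, not misclassified IgE, so it does not resolve the point.

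**The case against.** The strongest reply is that the threshold appears only in the legend of a conceptual model, inside a prediction. Specific IgE is not among the five mechanisms listed under Secondary study outcomes, and the mechanisms listed for atopy are measured by IL-10. The Analysis plan allows immunological variables to be log-transformed and continuous, and a fuller plan might handle IgE by level. This limits the reach of the point but does not remove it: the article does state a threshold, makes the figure a guide to analysis, and elsewhere gives a reason to distrust IgE just above that threshold.

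A second reply is that the bias needs a difference in cross-reactive IgE between exposed and unexposed children, which the article does not assert. Its statement concerns rural tropical children as a population. It calls the effect of maternal and early infant infection on specific IgE unclear, detected infections are treated, and the skin test comes at 5 years. This stands. A reader might infer that attenuation arises by construction; the documents do not support that, and at equal frequency there is none.

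A reader might also infer that the plan would take attenuation alone as proof of IL-10-mediated suppression. It would not: Figure 3 makes a joint prediction that includes the IL-10 link, and the study measures IL-10 responses to *D. pteronyssinus*, *P. americana* and *A. lumbricoides* antigen.

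Finally, 0.7 kU/L is the upper end of an example, not a proven limit of cross-reactivity. A case for making it the sole primary cut-off therefore cannot be built on this article.

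**Conclusion.** The point holds in conditional form. The threshold in Figure 3 conflicts with the article's own account of IgE at 0.35-0.7 kU/L. If cross-reactive IgE is more frequent in exposed children, which the Background makes plausible and the Discussion leaves unclear, the IgE-skin test association can look weaker in them with no mast-cell effect.

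Under the assumed inputs the spurious ratio is 0.51 at 20% versus 5%, within a range of about 0.39 to 1.0. These figures show how large the artefact could be; they do not estimate it for this cohort, because every frequency in the model is assumed.

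Only the secondary, mechanistic interpretation is exposed. A reader might extend the concern to the primary atopy analysis, but that outcome does not use IgE, and in both illustrations skin-test prevalence is the same in the two groups. The change is worth making but does not threaten the primary results.

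**What to change.** In the analysis of the IgE-skin test mechanism:
- keep > 0.35 kU/L as stated in Figure 3;
- repeat the analysis at >= 0.7 kU/L, and by IgE level using log-transformed specific IgE;
- attribute attenuation to mast-cell suppression only if it persists above the 0.35-0.7 kU/L band and is accompanied by the predicted link with IL-10.

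This is a change of analysis wording that uses the same IgE values. The cost is fewer IgE-positive children and wider intervals at the higher cut-off, including the loss of any truly sensitized children with IgE below it. A higher cut-off reduces the bias but may not remove it, since cross-reactive IgE may extend above 0.7 kU/L; the report should say so.
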